Primary health care use and chronic illness management	The National Health Insurance Service Registry (SSR)
Educational activities	Statistics Denmark (UDDA)
Delinquency and incarceration Parental delinquency and incarceration	The Danish Central Crime Register (KRAF) The Danish Central Crime Register (KRMS)
Prescription drug use	The Register of Pharmaceutical Sales (LSR)
Parental psychiatric illness, and substance use	National Patient Register (LPR) The Danish Health Data Authority
Disability services received	Handicap (HANDIC)
Neighbourhood effects, aggregated measures of: Unemployment Income Family types	Derived from above sources

Propensity scores are estimated using regularised logistic regression (11), or a low-depth random forest with *headspace* participation as a binary outcome. The matching will be done using the probability score and an optimal matching algorithm that will select the six closest matches with a caliper threshold at or below 0.25 on the log (odds) transformation of the propensity score. No replacements will be used. Missing values in predictors are handled by adding missingness indicator categories to categorical data and by replacing missing data with model-based imputations or slicing numerical variables in quantiles and then adding a categorical indicator of missingness. Matching will be carried out in two repeated batches with no overlap or cross-sample replacement. When all baseline data is collected, the matching is reiterated for the whole pool of cases and controls to ensure optimal balance on all matching parameters, at the cost of a smaller control group. The matching parameters will include all self-reported outcomes (e.g., wellbeing, loneliness) and register-based outcomes (e.g., number of hospitalizations or outpatient contacts). The statistical power obtained for numerical outcomes is above 0.98 for Cohen’s D at 0.15, even in the case of a reduction of controls to a 2:1 ratio in the final matching.

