### Data analysis

#### Sample size

A very conservative estimate of 1,900 participants with complete data at both baseline and follow-up (400 in *headspace* and 1,500 among controls), will provide 90% power to detect standardised mean differences of 0.18 in a two-sided *t*-test. This corresponds to 0.22 points on the WHO-5 Wellbeing Index, 1.16 points on the General Self-Efficacy scale and 0.36 points on Cantril’s Ladder. However, the statistical power might be degraded for analyses relying on multiple imputation because of the expected substantial proportion of missing data. The registry-based outcomes measured at 3 years of follow-up are unaffected by missingness and will have an expected 10,000 controls and 1,500 cases. This will provide statistical power sufficient for detecting small effect sizes, e.g., 83% power for detecting a 12.5 vs. 10% difference on a binary outcome.

Baseline characteristics for the two groups will be reported using means and standard deviations for numeric variables and count (n) with percentages for categorical variables. Mean difference from baseline to follow-up will be presented for both the *headspace* and the control group for all the included outcome measures. For normally distributed continuous outcomes a linear regression will be conducted to test the differences between the two groups. For non-normally distributed outcomes a proportional odds model will be used. The analyses for differences between groups will be adjusted for any baseline differences exceeding a predefined threshold. Moreover, subgroup analyses will be conducted where all analyses will be stratified for age (≥18 years). Missingness will affect the survey measures recorded at baseline and follow-up. Missing data will be handled using multiple imputations, possibly in combination with inverse probability weighting of observations (26). Imputation variables will be included from the complete (or near-complete) and co-occurring registry-based data observations as well as from all survey data collected up to the timepoint of the measure being imputed. A detailed statistical analysis plan (SAP) is also published and available at: https://archive.org/details/osf-registrations-9kzfd-v1.

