A potential pitfall in the effectiveness evaluation pertains to selection bias and the dynamics of outcomes before participation in the study (33). Young people’s mental health and wellbeing may be volatile with emotional ups and downs rather than persistent with the same levels of wellbeing over time, for instance shown in a study by Tegner Anker et al. (34). Youth would primarily seek help at “mental downturns,” that is at times with high level of emotional distress, there will be a regression to the mean, that might be difficult to identify in the control, thus posing a risk that natural improvements will be interpreted as effectiveness of the *headspace* intervention. While analysing the data, differences between the groups on all baseline outcomes will be tested for statistical significance. The analyses for differences between groups will be adjusted for any baseline differences with a *p*-value below 0.05.

Participants in the *headspace* group and the control group are matched on individual-level characteristics only. At the beginning of the data collection period, there were headspace centres in 22 out of the 100 municipalities of Denmark, meaning that it was not hard to identify controls. There were headspace centres is the four largest cities of Denmark (Copenhagen, Aarhus, Odense, and Aalborg) but not in some of the other larger cities such as Silkeborg or Kolding. There could be unobserved municipality-level factors potentially affecting the treatment effect estimates, e.g., related to urban density or distance to urban centres. We have, however, seen no substantial problems for the matching algorithm to identify comparable controls on the observed factors. We would also, from a pragmatic point of view, expect important municipality-level differences to be captured by the range of individual-level matching factors used (e.g., social status).

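### Missing baseline scores are to be imputed without the 6-month score, so baseline adjustment of the 6-month comparison is incomplete if a baseline gap survives matching

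*Protocol article*

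**What the plan says.** All of this concerns Study 1 of the protocol article.

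- **Where data are missing** (Data analysis, text under Sample size): "Missingness will affect the survey measures recorded at baseline and follow-up". Power of the imputed analyses may suffer "because of the expected substantial proportion of missing data". No percentage is given, and no split by wave.
- **Method** (same place): "Missing data will be handled using multiple imputations, possibly in combination with inverse probability weighting of observations".
- **Predictors** (same place): from registers, "Imputation variables will be included from the complete (or near-complete) and co-occurring registry-based data observations"; from the surveys, "all survey data collected up to the timepoint of the measure being imputed".
- **Survey waves** (Outcome measures at 6 months follow-up): two, at baseline and at 6 months.
- **Use of baseline scores in the outcome analysis** (Data analysis): "The analyses for differences between groups will be adjusted for any baseline differences exceeding a predefined threshold". Methodological challenges gives the trigger: "adjusted for any baseline differences with a *p*-value below 0.05".
- **Matching** (Procedures for matching the control group): "The matching parameters will include all self-reported outcomes (e.g., wellbeing, loneliness) and register-based outcomes". That section has its own rule for missing predictor values: missingness indicators, model-based imputation, or cutting into quantiles.

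**The concern.** For a missing 6-month score the time rule does no harm, because baseline comes earlier and stays in the imputation model. For a missing baseline score the rule removes the 6-month score, which is the outcome of the regression in which the imputed baseline will be a covariate.

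Values imputed without the outcome carry no association with it beyond what their predictors carry. Mixing them with observed values flattens the baseline slope, and the regression then subtracts too little of any baseline difference between the groups. What is left over is counted as an effect of headspace. This can happen even when baseline scores are missing completely at random.

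At stake is the adjusted 6-month comparison on the self-reported scales. Adjustment is triggered only when the groups differ at baseline, which is when the shortfall matters.

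**Working it through.** **The plan's own figure.** With 400 vs 1,500 complete cases, a standardised difference of 0.18 and two-sided alpha 0.05 (assumed, since alpha is not stated), SE = √(1/400 + 1/1500) = 0.0563. Then 0.18/0.0563 = 3.20, 3.20 − 1.96 = 1.24, and power is 89.2%. This agrees with the stated 90%, so 0.18 SD is a fair yardstick.

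**When adjustment starts.** At these numbers p < 0.05 needs an observed gap of about 1.96 × 0.0563 = 0.11 SD.

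**Inputs assumed, because the article does not give them.**
- Baseline/follow-up correlation β = 0.6.
- Correlation r between register predictor and baseline: 0.4, with 0.3 and 0.6 as alternatives.
- Share π of baseline scores missing completely at random: 20% or 40%.
- Baseline gap d (headspace minus control): −0.1, −0.3 or −0.5 SD.
- True effect zero; follow-up observed for everyone; exposure group in the imputation model; linear regression.

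**Formula.** Observed baselines (share 1 − π) carry the full slope. Imputed ones carry only what passes through the register predictor, a fraction r². Hence

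attenuated slope = β × [(1 − π) + π r²], and bias = d × (β − attenuated slope).

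Example with r = 0.4, π = 0.40, d = −0.5: the slope is 0.6 × (0.60 + 0.40 × 0.16) = 0.398, and the bias is −0.5 × (0.600 − 0.398) = −0.101 SD.

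| r | π | slope | bias, d = −0.1 | d = −0.3 | d = −0.5 |
|---|---|---|---|---|---|
| 0.3 | 20% | 0.491 | −0.011 | −0.033 | −0.055 |
| 0.3 | 40% | 0.382 | −0.022 | −0.066 | −0.109 |
| 0.4 | 20% | 0.499 | −0.010 | −0.030 | −0.050 |
| 0.4 | 40% | 0.398 | −0.020 | −0.060 | −0.101 |
| 0.6 | 20% | 0.523 | −0.008 | −0.023 | −0.038 |
| 0.6 | 40% | 0.446 | −0.015 | −0.046 | −0.077 |

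**Simulation check** (400 vs 1,500, five proper imputations per data set).
- At r = 0.4 (200 replicates per cell, Monte Carlo SE about 0.0035), the slope was 0.50 at 20% missing and 0.40 at 40%. The biases were −0.03 and −0.06 SD at a gap of −0.3, −0.05 and −0.10 at −0.5, and −0.01 to −0.02 at −0.1.
- At r = 0.3 and 0.6 (150 replicates per cell), the slopes were 0.49 and 0.38, and 0.52 and 0.45, as the formula gives.
- With d = 0 the bias was zero apart from simulation noise.
- With the 6-month score added to the imputation model, the slope returned to 0.60 and the bias was within about 0.005 SD of the full-data estimate throughout.

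**When follow-up is missing too** (r = 0.4, 300 replicates, Monte Carlo SE 0.004 to 0.005).
- If 80% of those missing baseline also miss follow-up, the bias at gaps of −0.3 and −0.5 is −0.017 and −0.022 SD with 20% of baselines missing, and −0.035 and −0.053 SD with 40%.
- If all of them miss follow-up, and half of the others do too, it lies between −0.007 and +0.001 SD, which is zero within simulation error.

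**The case against.** The case on the other side is about size, and most of it stands.

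- **Who contributes.** Only people with baseline missing and follow-up observed create the bias. Under Study sample, headspace users log in, consent and fill out questionnaires, and their first recorded measurement must be their first session. Their gaps may therefore fall mainly at follow-up.
- **The gap may be small.** The final matching uses the self-reported outcomes and gives up controls to gain balance. A reader might infer from the remarks in Methodological challenges on help-seeking at low points that the matched groups will differ at baseline by 0.3 to 0.5 SD. The article does not say so; the same section describes controls as sharing the participants' wellbeing. Near the 0.11 SD trigger the bias is only 0.01 to 0.02 SD.
- **Matching.** A reader might infer that the time rule also spoils the matching. Matching has its own missing-value rule, and the final matching takes place once baseline data are in, when 6-month scores need not exist.
- **Exposure group.** Nothing says it is left out of the imputation model, and that omission is not alleged here.

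The objection does not remove the defect. The article still plans for significant residual baseline differences, and it states the predictor rule outright rather than leaving it to the SAP, which was not available for this review. The restriction offers no gain to set against the bias.

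**Conclusion.** The rule is wrong as written for one use: imputing a missing baseline score that then serves as a covariate in the 6-month regression. The mechanism is certain; the size cannot be fixed from the article.

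For 20% to 40% of baselines missing, under the assumptions above with r = 0.4 and all follow-up observed, the bias runs from about −0.01 SD (gap −0.1) to −0.10 SD (gap −0.5), against a 0.18 SD target. It is roughly half that if most people missing baseline also miss follow-up, about zero if all do, and zero without a residual gap.

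A reader might infer that the plan loses about half its target effect. That needs the largest gap, the heavier missingness and complete follow-up together, and the article supports none of the three. Nor is bias inevitable whenever data are missing completely at random, since a residual gap is also needed. If headspace users start lower, the error understates benefit rather than creating a false positive. The figures are for linear regression; the proportional odds analyses were not computed.

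**What to change.** For the imputation that feeds the 6-month outcome analysis, delete the limit to survey data up to the time of the measure. State instead that baseline and 6-month scores are imputed jointly from both survey waves, exposure group and register data, in a model compatible with the analysis model. Align the SAP if it carries the same rule.

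Leave any imputation used for matching under its own rule; it need not use the 6-month outcome.

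The cost is one sentence in the plan and a small change to the imputation code. No new data are needed, and the stated power figures do not change.

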## Study 2: economic evaluation

The aim of the economic evaluation is to evaluate the cost-effectiveness of *headspace*, compared with a matched control group. The evaluation takes on a health care perspective when considering the costs of *headspace*, including intervention and health care costs. The study uses the same cohort as in the effectiveness evaluation, described above.

### Outcome

Outcome for the cost-effectiveness analysis will be weeks in competitive employment or education during follow-up.

### Costs

The total costs of individuals in contact with *headspace* including intervention costs will be estimated and compared with the costs of individuals in the control group. Non-parametric bootstrapped *t*-test analysis will be used to estimate the statistical significance of the cost difference between *headspace* participants and controls. Mean costs and *p*-values will be reported to show a statistically significant difference between the groups. Intervention costs will be estimated by using information on operating costs from the *headspace* centres.

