### Cost-effectiveness analyses

The time horizon of the evaluation will be 3 years from the first contact to *headspace*. To evaluate cost-effectiveness, the incremental cost-effect ratio (ICER) will be estimated (27). The ICER represents the cost differences between the *headspace* group and the control group divided with differences in outcome measured by labour market contact/educational attainment. Nonparametric bootstrapping will be used to estimate confidence intervals of the mean differences of the groups. Predicted ICERs will be depicted on cost-effectiveness planes to show uncertainty therein. A cost-effectiveness acceptability curve will be generated to assess the probability of *headspace* being cost-effective when the decision-maker is willing to incur additional costs for an extra point increase in outcome up to a given threshold.

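### The cost difference and the ICER are compared without adjustment for pre-index cost, which gives up precision and leaves them open to any prior-cost imbalance that survives matching

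*Protocol article*

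**What the plan says.** In the protocol article, Study 2, Costs, a bootstrapped t-test "analysis will be used to estimate the statistical significance of the cost difference between" the two groups, reported as mean costs with p-values. Under Cost-effectiveness analyses, "Nonparametric bootstrapping will be used to estimate confidence intervals of the mean differences of the groups", and these differences form the ICER, the cost-effectiveness plane and the acceptability curve. The horizon is long: "The time horizon of the evaluation will be 3 years from the first contact to" headspace. No covariate or regression model is named in Study 2.

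The opening of Study 2 states: "The study uses the same cohort as in the effectiveness evaluation, described above". For that cohort, Study 1 has an adjustment rule: under Data analysis, group comparisons are to be "adjusted for any baseline differences exceeding a predefined threshold". Methodological challenges gives the criterion as a baseline p-value below 0.05. Study 2 does not repeat or refer to this rule.

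Table 1 lists prior psychiatric contacts, general health-care use, primary-care use and prescription drugs as matching variables. Table 2 draws hospital, primary-care and prescription costs from the National Patient Register, the national health service register and the national prescription data.

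**The concern.** In a non-randomised comparison of skewed costs, prior cost is an obvious predictor of later cost. A plain two-group test does not use it. Two things follow. The interval around the cost difference is wider than it needs to be. And if the groups still differ in prior cost after matching, that difference passes, in proportion to the correlation, into the ICER numerator and the acceptability curve.

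Matching is on a single propensity score within a caliper, and its inputs are use and contacts, not tariff-valued cost. Similar counts do not guarantee similar mean cost when a few people are very expensive.

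There is also an internal mismatch. Weeks in work or education is both a 3-year outcome of Study 1, where the adjustment rule applies, and the effect measure of the ICER, where no adjustment is named. The same outcome could therefore be reported adjusted in one study and crude in the other.

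**Working it through.** **The plan's own figures.** The article gives no power, SD or effect size for costs. The nearest figure is for register outcomes, which "will have an expected 10,000 controls and 1,500 cases", with "83% power for detecting a 12.5 vs. 10% difference on a binary outcome". At two-sided alpha 0.05 (assumed), with 12.5% in the headspace group:
- pooled proportion = (187.5 + 1,000)/11,500 = 0.1033; null SE = 0.00843; alternative SE = 0.00905
- power = Φ[(0.025 − 1.96 × 0.00843)/0.00905] = 82.6%, which reproduces 83%.

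The survey calculation, which "will provide 90% power to detect standardised mean differences of 0.18 in a two-sided" t-test with 400 and 1,500 people, gives 89.2% and also reproduces. No stated number is wrong.

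**Precision.** In units of the cost SD, the unadjusted SE is √(1/1,500 + 1/10,000) = 0.0277. The difference detectable with 80% power is (1.960 + 0.842) × 0.0277 = 0.078 SD. Adjusting for a baseline cost with correlation ρ multiplies the variance by 1 − ρ². The values of ρ are assumed.

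| ρ | Variance removed | SE multiplier | Detectable difference, 10,000 controls | Detectable difference, 3,000 controls |
|---|---|---|---|---|
| none | 0% | 1 | 0.078 SD | 0.089 SD |
| 0.3 | 9% | 0.954 | 0.074 SD | 0.085 SD |
| 0.5 | 25% | 0.866 | 0.067 SD | 0.077 SD |
| 0.6 | 36% | 0.800 | 0.062 SD | 0.071 SD |

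The last column uses the 2:1 ratio that the article allows for after final matching. A lognormal simulation (1,500 against 9,000) gave SE ratios of 0.945, 0.854 and 0.670 at correlations of 0.33, 0.54 and 0.75, close to √(1 − ρ²), so skewness does not undo the result. The formula treats the groups as independent samples. Where matching already makes prior cost similar within sets, the gain is somewhat smaller.

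**Bias, if imbalance remains.** Bias = ρ × imbalance in prior cost. For an assumed imbalance of 0.05 SD and 10,000 controls:
- ρ = 0.3: 0.015 SD, or 0.54 SE; type I error 8.4%
- ρ = 0.5: 0.025 SD, or 0.90 SE; type I error 14.7%
- ρ = 0.6: 0.030 SD, or 1.08 SE; type I error 19.2%

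With zero imbalance the bias is zero.

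**Would the Study 1 rule catch it?** A baseline difference reaches p < 0.05 only from about 1.96 × 0.0277 = 0.054 SD. An imbalance of 0.05 SD lies below that, so a significance-triggered rule would often miss it.

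**How far adjustment helps.** In the simulation with the groups made to differ in latent need (correlation 0.54), adjusting for pre-index cost cut the bias from 0.030 to 0.014 SD. It did not remove it.

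**The case against.** The strongest reply is that the design already deals with prior use. The propensity score includes hospital, psychiatric, primary-care and prescription use. Matching is reiterated on the whole pool once baseline data are in, with register outcomes among the parameters, and repeated with updated data before the 3-year analyses. This stands. A reader might infer that the cost difference is biased; the article shows no residual imbalance, and the 0.05 SD used above is only an illustration.

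A reader might also infer that the bootstrap resamples individuals and ignores matched sets. The article does not state the resampling unit, and that detail can sit in the SAP, which is not shown. Nor can one infer that cost and weeks are drawn separately: each point on a cost-effectiveness plane is a cost-effect pair, so joint draws are implied.

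It is also fair that pre-index cost is not shown to be available for everyone and every item. The article lists prior use, not cost, provides for missing predictors, and says some registers lag at matching. The primary-care and prescription sources carry slightly different names in Tables 1 and 2; I take them to be the same data. The case is good for these three health-care components and weaker for the labour-market, social-service, justice and tax items.

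Finally, the precision gain at a correlation of 0.3 is small, and the SAP could already specify adjustment. What remains is that the article names a method, and that method as named has no covariate.

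**Conclusion.** The point holds as a worthwhile improvement to a stated method. It is not an arithmetic error or a demonstrated bias. The precision loss is real for any correlation above zero: small at 0.3 (SE 5% smaller with adjustment) and material from about 0.5 (13%, rising to 20% at 0.6). The exposure to imbalance is a risk of unknown size. It is nil if matching balances prior cost, and about half to one standard error if 0.05 SD remains at correlations of 0.3 to 0.6. These sizes rest on assumed correlations, an assumed imbalance, two-sided alpha 0.05 and controls treated as independent. The conclusion that baseline cost can be built covers hospital, primary-care and prescription costs, which match the health care perspective that Study 2 declares.

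**What to change.** Prespecify the cost difference as the group coefficient from a bootstrapped regression of 3-year cost on group and health-care cost in the 12 months before index, valued from the same hospital, primary-care and prescription registers. Include that covariate regardless of any baseline significance test; borrowing the Study 1 trigger would often leave it out. Use the adjusted differences in the ICER, the plane and the acceptability curve, so that weeks in work or education are not adjusted in Study 1 and crude in Study 2. Preferably resample whole matched sets, and say so.

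The cost is one pre-index costing step, possibly a further register extract for that year, and slightly more analysis. No new data collection from participants is needed. The report should state that adjustment reduces confounding by prior need but cannot remove the part that is unmeasured, including help-seeking.

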### *headspace* centres

*headspace* Denmark consists of 30 *headspace* centres and one national chat centre. All centres offer free counselling to young people between 12 and 25 years. The *headspace* centres are staffed with one cross-centre manager (one manager serves about three *headspace* centres), two paid counsellors, volunteer counsellors, and two part-time (15 h. per week) assertive professionals employed in the local mental health services and/or social services. The *headspace* centres are located so they are accessible to young people (for instance close to public transportation). The centres furniture and decorations signal a youth-friendly atmosphere. The *headspace* centres are open 3 days a week, between 12 and 18 (12 AM to 6 PM) and the chat centre is open between 12 and 22 (12 AM to 10 PM).

Training of counsellors involves an online training program, a weekend course, and on-site training and supervision with experienced counsellors and professionals. The counselling provided to the youth is delivered in an open-minded, curious, and flexible approach, and the counsellors are guided by a person-centred approach that sets the young person’s needs at the centre of their work. Volunteering is a key principle in the *headspace* organisation, and young people seeking counselling and support are informed that most counsellors are volunteers.

Young people accessing counselling do not need to state their name or personal ID number, so their identity remains anonymous. The *headspace* centres operate under the motto “Nothing is too big or too small,” meaning that all young people in the targeted age group can access the centres. Should the young person require additional support such as a mental health assessment, specialist treatment or support from social services, the counsellors can offer support and guidance in accessing these services. In addition to counselling and bridging to other services, *headspace* centres play an active role in providing information about youth mental health, de-tabooing mental health problems among young people, as well as making *headspace* centres visible and thus accessible through community engagement and collaborations with schools, etc.

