### Register data

All data will be drawn from Danish national registers. The study will include information on health care services (somatic and psychiatric inpatient and outpatient care, including emergency services and diagnosis related groups (DRG), general practitioners, dentists and other medical specialists, medical prescriptions) and social services. Differences in utilisation of health care will be reported in natural units and costs, while differences in utilisation of social services will be reported in natural units. All elements included in the analyses are described in more detail in Table 2.

**Table 2 tab2:** Components included in the economic evaluation.

Costs	Definition	Source
Hospital costs	Inpatient, outpatient, and emergency room contacts in somatic and psychiatric hospitals, valued with Danish national diagnosis-related groups (DRG)-tariffs.	The National Patient Register with DRG and outpatient tariffs (37, 38).
Primary healthcare costs	Contacts to general practitioners, practising specialists and other health care professionals reimbursed (or partly reimbursed) by the Danish National Health Service, e.g., dental care or psychological treatment. Costs are valued with national service tariffs.	The National Health Service Register (39).
Prescription pharmaceuticals	The full price (regardless of subsidies etc) of prescription drugs purchased in Danish pharmacies.	The Pharmaceutical Database (40).
Transfer payments	Cash benefits, early retirement pension, education benefits, other transfers	DREAM database
Costs of labour market interventions	All interventions initiated by the municipal job centres: counselling, mentor support or vocational rehabilitation interventions.	Data will be obtained from the Danish Agency for Labour Market and Recruitment.
Social service costs	Alcohol abuse treatment; drug abuse treatment, day-care; drug abuse treatment; temporary housing; long-term housing; soc. support in housing; public housing; soc.pæd. Support in one’s own home; subsidies for personal and practical help; disability assistance scheme; companion scheme; sheltered employment or activity; and social services	Data will be obtained from Statistics Denmark
Intervention costs	Costs of a counselling session at headspace will be calculated	Data will be obtained from headspace Denmark.

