### Mechanisms of impact

Mechanisms of impact are defined as “the intermediate mechanisms through which intervention activities produce intended (or unintended) effects” for the individual service user (29). This study will describe possible mechanisms by which the key activities might create effects on service users’ loneliness, wellbeing, self-efficacy, and mental health (see Figure 1). The study will emphasise the perspectives of the service users and investigate their (possible) progression after engaging with *headspace.* If feasible, service users will be interviewed twice. The first interview is expected to take place right after the first counselling session. Previous evaluations have shown that service users engage in 2.7 counselling sessions on average (15). Follow-up interviews are expected to be conducted after the last counselling session and on average 4 months after the first session. This relatively short follow-up time (compared to study 1) will ensure that experiences regarding *headspace* are not too far away in memory and thus provide longitudinal information about the life course of each service user and their experienced benefits (or negative experiences from interacting with *headspace* personnel).

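### The named source for the intervention cost does not visibly cover the assertive professionals, who work in every centre but are employed by local health or social services

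*Protocol article*

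**What the plan says.** Study 2 states: "The evaluation takes on a health care perspective when considering the costs of" headspace, and it counts both intervention and health care costs. Under Costs: "Intervention costs will be estimated by using information on operating costs from the" headspace centres. Table 2 (Register data) gives the unit, "Costs of a counselling session at headspace will be calculated", and the supplier, "Data will be obtained from headspace Denmark". No regional or municipal payroll source appears for this cost line.

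The section on the headspace centres lists the staff of each centre. They are a share of a manager ("one manager serves about three" centres), two paid counsellors, volunteers, and "two part-time (15 h. per week) assertive professionals employed in the local mental health services and/or social services".

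The Introduction sets the standard for the economic study: a cost-effectiveness result in which every relevant cost is measured.

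**The concern.** Part of each centre's standard staffing has an employer other than headspace, while the intervention cost is built only from headspace's own figures. On a plain reading, an input that the article itself lists may fall outside the costing rule.

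The intervention cost enters only the headspace arm, so an input left out of it is not balanced by a matching omission among the controls. Staff employed by mental health services fall within the declared health care perspective. Staff employed by social services belong in the total as inputs to the intervention. What is at stake is the cost difference, and through it the incremental cost-effectiveness ratio (ICER) and the acceptability curve on which policymakers are meant to rely.

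**Working it through.** The article gives no wage, session cost, cost difference or ICER, so there is no figure of its own to reproduce. What can be checked is whether another cost line would pick up this time, how large the input is in hours, and which way an omission would act.

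**1. Could another line of Table 2 recover the time?** Hospital and primary care costs are individual contacts valued at DRG or service tariffs. Nothing in the article suggests that work inside a headspace centre produces such a contact. For social services the text says that "differences in utilisation of social services will be reported in natural units", so that route would not yield a cost either, although Table 2 also carries a row for social service costs. No line visibly recovers the time.

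**2. Inputs per centre per week**
- External hours: 2 professionals x 15 h = 30 h (headspace centres section).
- Counsellors: 2 x h. The hours are not stated. Assumed range: h = 18 (the opening hours, 3 days x 6 h) to h = 37 (an assumed full-time week).
- Manager: one per about three centres. With an assumed 37-hour week, 37/3 = 12.3 h.

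**3. Share of paid staff hours outside headspace employment** = 30 / (2h + 12.3 + 30)
- h = 37: 30 / (74 + 12.3 + 30) = 30 / 116.3 = 26%
- h = 18: 30 / (36 + 12.3 + 30) = 30 / 78.3 = 38%
- If 15 h is the total for both professionals, with h = 37: 15 / (74 + 12.3 + 15) = 15 / 101.3 = 15%

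**4. From hours to cost, on further assumptions.** If all 30 h lie outside the operating costs and hourly wages are equal, adding them raises staff cost by 30 / (2h + 12.3):
- h = 37: 30 / 86.3 = 35%
- h = 18: 30 / 48.3 = 62%

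If staff make up 50% to 90% of operating costs (assumed), the intervention cost rises by between 0.5 x 35% = 17% and 0.9 x 62% = 56%. If headspace already carries the time in its accounts, the rise is 0.

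**5. Direction.** Let k > 0 be the omitted cost per participant, dC the true cost difference, dE the effect difference and L the willingness to pay. Estimated net benefit is L x dE - (dC - k), which is k above the true value whatever the sign of dE. The acceptability curve is therefore too high, or at best unchanged, at each L. The estimated ICER is (dC - k) / dE. It falls by k / dE, so it looks better for this reason only when dE is positive.

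**The case against.** The strongest reply is that the article does not say these staff are excluded. It names their employer but not who finally bears the cost. It counts them among the centres' staff, and it does not define operating costs. A reimbursement arrangement would place them inside the figure. This stands: a reader might infer that the costing definitely leaves them out and that the cost is understated, but the text supports only the conditional form.

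A second reply is that a journal article need not itemise a cost. That is fair in general. Here, however, the article itself fixes the source and the sole supplier, and separately describes an input that this source does not visibly hold. The point rests on what is stated, not on missing detail.

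Third, the percentages in steps 2 to 4 rest on assumed working weeks, and those in step 3 are shares of hours. They ignore wage differences, premises, training and central costs, and the cost difference also contains three years of health care use. This stands. Operating costs may also include community engagement, which could raise the calculated cost per session. So the direction given here applies to this one component and not to the session cost as a whole.

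A reader might also infer that every participant will be charged an average number of sessions, because the process evaluation says "Previous evaluations have shown that service users engage in 2.7 counselling sessions on average". The article does not support this. That figure is cited to time the interviews in Study 3, and a per-session cost in Table 2 is consistent with unit cost multiplied by each person's own sessions. Counselling is open to anonymous users, but study participants register their personal ID, so anonymity does not rule out individual costing.

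**Conclusion.** The concern holds in conditional form. The stated source for the intervention cost does not visibly cover 30 h a week per centre of staff whom the article lists as standard. This is about 26% to 38% of paid hours under the assumed working weeks, and about 15% if 15 h covers both professionals and counsellors work 37 h. If the hours are omitted, the headspace arm's cost is understated, and its net benefit and probability of cost-effectiveness are overstated. If headspace already books or reimburses the time, nothing changes. The size of any effect on the ICER cannot be calculated from the article, and a more favourable ICER would follow only with a positive effect difference. The possible gap is large enough, and cheap enough to close, that the plan should settle it before the costs are compiled.

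**What to change.** Define the intervention cost as headspace operating costs plus the assertive professionals' hours, valued at public-sector salary cost obtained from the employing services. State whether 15 h a week is per person or for both, and whether headspace reimburses any of it, and count any reimbursement once. Spread the added cost over sessions by the same rule as the operating costs. Report the cost difference, the ICER and the acceptability curve with and without this component.

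The price is one additional cost figure from the employing services and a somewhat higher stated intervention cost. No participant data need to be collected, so the change can still be made although recruitment has begun.
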